### 2.11. Ethics

The Institutional Review Board of Kyung Hee University Korean Medicine Hospital has approved the protocol (IRB approval numbers KOMCIRB 2020-12-002-001). This study was registered in the national clinical trial registry Clinical Research Information Service, a primary registry of the World Health Organization International Clinical Trials Registry Platform (KCT0006252).

### 2.12. Statistical Analysis

For assessing the feasibility of this study design, we will analyze the subject recruitment rate, dropout rate, and dropout reasons. The subject recruitment rate will be calculated by dividing the total number of study subjects by the total number of participants screened (%). The dropout rate will be calculated for all participants and each herbal medication group. The dropout reasons will also be assessed. For continuous variables that will be assessed to evaluate the potential clinical effectiveness of herbal medications, the standard deviation, median, minimum, and maximum values for each time point will be presented. An analysis of covariance (ANCOVA) test will be conducted for differences between herbal medication groups (*p* < 0.05). If the assumption of ANCOVA is tested and the basic assumptions such as normality and equal variance of data are violated, the Kruskal–Wallis test will be performed. Statistical analysis will be conducted using the R-software (R 4.1.2, The R Foundation, www.r-project.org, accessed on 9 August 2022) or Jamovi software (Version 1.8.0, The jamovi project, www.jamovi.org, accessed on 9 August 2022). A full analysis set will be used to analyze variables for effectiveness evaluation. Data on safety evaluation will be used with the safety set. All statistical tests, unless otherwise defined, are tested with the two-sided test, with a 5% significance level.

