### 2.3. Sample Size

The current study is a phase 2 preliminary clinical study, thus we will recruit 45 patients without sample size calculations. Fifteen patients will be assigned to each of the three intervention groups. The results from this study will be used to calculate the sample size for further confirmatory clinical trials.

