### 2.6. Blinding and Treatment Allocation

Due to the design characteristics of this clinical study without a control group, randomization, allocation concealment, and blinding will not be implemented. The investigator shall assign each patient a unique patient number at visit 0 (V. 0). To allocate patients to each herbal medicine group, the KM syndrome differentiation will be conducted by an internal medicine specialty Korean Medicine doctor (KMD) with a clinical experience of >10 years. According to the main sequelae symptoms after COVID-19, patients will be allocated to the fatigue or cognitive dysfunction group and then assigned to the appropriate herbal medicine intervention group based on each sub-syndrome differentiation pattern. The considerations for syndrome differentiation are shown in Table 2.

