##### Checklist Individual Strength (CIS)

CIS is an indicator for evaluating fatigue in the last 2 weeks, and will be accessed by patients themselves using a questionnaire as instructed by the principal investigator or other researchers at visits 2, 3, 4, 5, and 6. Each patient will answer the CIS questionnaire after receiving sufficient explanation about its purpose and method from the clinical investigator [5]. The total CIS score will be compared among the intervention groups for each visit.

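### Each herb is tied one-to-one to a symptom pattern, so the planned tests between herb groups on the clinical scales cannot estimate a herb effect

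*Protocol article*

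**What the plan says.** **Allocation (protocol article, 2.6, 2.7 and Table 2).** There is no control group, and "randomization, allocation concealment, and blinding will not be implemented". A Korean Medicine doctor first sorts patients by main symptom, fatigue or cognitive dysfunction. Patients are then "assigned to the appropriate herbal medicine intervention group based on each sub-syndrome differentiation pattern". Section 2.7 and Table 2 set out three pairs:

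- CV1: fatigue with spleen-lung qi deficiency, given Bojungikgi-tang
- CV2: fatigue with dual qi and yin deficiency, given Kyungok-go
- CV3: cognitive dysfunction, given Cheonwangbosim-dan

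A patient who continues treatment receives the same product again.

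**Size (2.3).** "we will recruit 45 patients without sample size calculations", and "Fifteen patients will be assigned to each of the three intervention groups".

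**Analysis (2.12).** For the continuous effectiveness variables, "An analysis of covariance (ANCOVA) test will be conducted for differences between herbal medication groups". The covariate is not named. Kruskal–Wallis replaces ANCOVA if "basic assumptions such as normality and equal variance of data are violated". On level: "All statistical tests, unless otherwise defined, are tested with the two-sided test, with a 5% significance level".

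**Where it applies (2.8.2).** For CIS, "The total CIS score will be compared among the intervention groups for each visit". Similar sentences cover ChFS, EQ-5D-5L, PSQI-K, K-MoCA, CFQ, BDI, digit span and K-BNT-15. No within-group test is named, so the between-group test is the only inferential method stated for these scales.

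**The concern.** The test is framed as a comparison of herbal medication groups, within an analysis meant to assess the potential effectiveness of the herbs. A reader will take a significant result to mean that one herb did better than another. The design cannot support that reading, because patients on different herbs were put there for having different presentations.

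There is a second, conditional problem. If the presentations start at different levels on a scale, or recover differently without treatment, the test can exceed its nominal 5% when all three herbs are inert.

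Sections 2.1 and 2.3 say the results will inform later confirmatory trials. A between-group difference misread as a herb difference could be carried into that planning.

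**Working it through.** **1. The plan's own figure.** 3 groups × 15 = 45, as stated. No power or effect size is given, so there is nothing further to reproduce.

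**2. Aliasing.** Cross three patterns with three herbs: 3 × 3 = 9 cells, of which only 3 are filled. Separate pattern and herb effects need 2 + 2 = 4 degrees of freedom between groups, and three groups supply 2. The contrast of CV3 with CV1 estimates

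(herb 3 − herb 1) + (pattern 3 − pattern 1),

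and only the sum is observable. Baseline or any other covariate leaves the two group indicators identical. This step uses only 2.6, 2.7 and Table 2.

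**3. What baseline adjustment leaves behind.** Assumptions that are not in the documents:

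- the covariate is the baseline score
- no patient truly changes
- CV3 differs from CV1 and CV2 by *d* SD in true baseline mean
- within-group retest correlation is *r*
- each group regresses to its own mean

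The raw follow-up difference is then *d*, the pooled within-group slope is about *r*, and the adjusted difference is

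*d* − *r* × *d* = (1 − *r*) × *d*.

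For *d* = 1 SD:

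| *r* | Adjusted difference with no herb effect |
|---|---|
| 0.5 | (1 − 0.5) × 1 = 0.50 SD |
| 0.6 | (1 − 0.6) × 1 = 0.40 SD |
| 0.7 | (1 − 0.7) × 1 = 0.30 SD |
| 0.8 | (1 − 0.8) × 1 = 0.20 SD |

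**4. Rejection rates.** Simulation of 3 × 15 patients with zero herb effect. The test is the ANCOVA F on 2 and 45 − 4 = 41 degrees of freedom, critical value 3.23.

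| Baseline gap, CV3 versus the others | ANCOVA rejection, *r* from 0.8 down to 0.5 |
|---|---|
| 0 | about 5% |
| 0.25 SD | 5–7% |
| 0.5 SD | 6–10% |
| 1.0 SD | 12–27% |
| 1.5 SD | 18–46% |

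Independent runs agree within about 2 percentage points.

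**5. Different untreated course.** With equal baselines but CV3's untreated recovery differing by 0.5 SD, rejection is 36–38% at *r* = 0.6. It is 31% at *r* = 0.5, 45% at 0.7 and 61% at 0.8.

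**6. Fallback.** Kruskal–Wallis takes no covariate. On follow-up scores it rejects in about 23%, 75% and 98% of trials at baseline gaps of 0.5, 1.0 and 1.5 SD. On change scores it stays near 5% under the same gaps, but at *r* = 0.7 it rejects in 38% when untreated course differs by 0.5 SD. The article does not say which score would be ranked.

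**The case against.** The strongest case against is about certainty and weight, and much of it stands.

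- **A reader might infer that ANCOVA will return false herb differences in this trial.** The documents do not support that. They give no SDs, no baseline means by pattern, no retest correlations and no natural history. With equal baselines and courses the test holds about 5%, and at a gap of 0.25 SD the excess is trivial. If all patients regress to a common mean, baseline adjustment leaves no spurious difference. Baseline is not even named as the covariate.
- **A reader might infer that every scale differs between groups by design.** Allocation uses main symptom, associated symptoms, tongue, pulse and stool, not scale scores. Every patient, CV3 included, must exceed 76 on CIS, so a CIS gap cannot be presumed. A gap is plausible mainly for CV3 against CV1 and CV2 on fatigue and cognition scales.
- **A reader might call the groups different illnesses.** All have post-COVID sequelae, and the Discussion puts fatigue and cognitive dysfunction in one category. CV1 and CV2 are two patterns of one main symptom.
- **A reader might infer that a herb will be picked for the next trial by p-value.** No passage says so. Section 2.3 speaks of sample size calculation.
- **The study is candid about its status.** Section 2.1 calls it preliminary, 2.6 discloses the lack of randomisation, and the Discussion says randomised trials are needed.

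None of this touches the aliasing. Even a test that holds exactly 5% gives a p-value that cannot be assigned to a herb. The general call for randomised trials does not tell the reader that these particular comparisons carry no herb interpretation.

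**Conclusion.** The point holds in two parts of different strength.

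**Certain, from the documents alone:** herb and pattern coincide completely, so neither the ANCOVA nor its fallback can estimate a herb effect on any clinical scale. A later analysis plan cannot repair this by choosing covariates.

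**Conditional, on assumed values:** the test may also reject too often with inert herbs. The excess runs from none to large, depending on baseline gap, retest correlation, untreated course and the regression model. It should be presented as a range, not as a property of this trial.

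The defect lies in secondary comparisons of a preliminary 45-patient study. It should be corrected, but it does not invalidate the study. The primary success rate in 2.8.1 is presented by symptom group with no between-herb test stated, and is unaffected. Comparing medication adherence by product is a legitimate feasibility question and is also outside this point.

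**What to change.** In 2.12, and in the 2.8.2 sentences on the clinical scales (CIS through K-BNT-15, not medication adherence):

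1. Remove the hypothesis test between herb groups, including the Kruskal–Wallis fallback.
2. Report change from baseline within each group with a confidence interval, with the three groups side by side.
3. Label each group as pattern plus herb, not by herb alone.
4. Add one sentence: herb is determined by symptom pattern, so differences between groups cannot be attributed to the herb.

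The cost is wording only, with no new patients, visits or measurements. What is lost is a set of between-herb p-values that had no valid herb interpretation. The within-group changes are uncontrolled and do not show efficacy either. If a later trial is to compare herbs, patients with the same pattern would have to be randomised between them.

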## 3. Discussion

With the continuously progressing global COVID-19 pandemic, medical care for the long-term effects of SARS-CoV-2 infection should be established. Long-term sequelae refer to persistent symptoms or signs for >6 months after COVID-19 recovery. According to a survey in Korea, 65.7% of responders who suffered from COVID-19 had long-term sequelae. The most common long-term sequelae are fatigue, followed by neuropsychiatric symptoms, such as concentration difficulty, amnesia, cognitive dysfunction, anxiety, and depression [13]. Furthermore, even some non-hospitalized COVID-19 patients have been reported to suffer from sequelae, such as fatigue, shortness of breath, cognitive dysfunction, and stress/anxiety at least once within 30 days or longer [14]. These neuropsychiatric symptoms and signs, such as fatigue and cognitive dysfunction after COVID-19, are considered a category of chronic fatigue syndrome/myalgic encephalomyelitis (CFS/ME). Indeed, several viruses are associated with CFS/ME, such as hepatitis C virus, human immunodeficiency virus, and Epstein–Barr virus [15]. These neurological complications have been suggested to be caused by a disturbance in neuroimmune regulation. The reduced anti-inflammatory cytokine (IL-10) level observed in the cerebrospinal fluid (CSF) may be related to neurological complications in patients with CFS/ME [16,17], and abnormal cytokine levels due to immune responses in SARS-CoV-2 infection have been reported to potentially contribute to the development of neurological complications, such as CFS/ME [18]. Furthermore, autopsy demonstrates SARS-CoV-2 may cause neuropathological lesions both in the parenchyma and vessels of the brain [19]. It also supports the theory that SARS-CoV-2 invades the choroid plexus epithelium, thereby resulting in leakage of the blood-CSF barrier [15]. In contrast, the finding of paucity of neuroinflammatory changes and absence of SARS-CoV-2 viral RNA in CSF of COVID-19 patients with neurological complications does not provide evidence of neuroinflammation in pathogenesis of SARS-CoV-2 [20]. Hence, the exact cause of neuropsychiatric sequelae in COVID-19 is still obscure, a conventional treatment for the sequelae has not yet been established, and symptomatic treatment and lifestyle management are being implemented. As the prevalence of these sequelae is expected to further increase as the spread of COVID-19 continues, related further studies are necessary.

Bojungikgi-tang (CV1), herbal medicine that will be administered to the fatigue group in the present study, has been investigated as the most frequently prescribed herbal medicine for the treatment and management of chronic fatigue by KMDs [21], and our systematic literature review reveals that Bojungikgi-tang has a significant effect in alleviating the symptoms of CFS compared to health supplements or symptomatic treatments. [22]. In addition, Kyungok-go (CV2), to be prescribed to another fatigue group, is used to improve physical fatigue, malaise, and residual symptoms after disease in KM clinical practice, and is one of the herbal medicines most prescribed to patients in the COVID-19 KM telemedicine program [23]. An animal study also provided evidence that Kyungok-go shows a significant improvement in exercise capacity and anti-fatigue properties by reducing the lactate level, enhancing the blood glucose level, and increasing glycogen in the skeletal muscles [24]. Cheonwangbosim-dan (CV3), the herbal medicine to be administered for cognitive dysfunction in this study, has reportedly been effective for memory improvement in an Alzheimer’s disease mouse model by inhibiting acetylcholinesterase, reducing hippocampal infarction, and suppressing proinflammatory cytokine production such as IL-1β and TNF-α [25]. Therefore, the results of these studies indicate that the herbal medicines to be administered in the present study have the possibility to mitigate fatigue and cognitive dysfunction after COVID-19 recovery.

A recent study on patients with convalescent COVID-19 found that most patients had SARS-CoV-2-specific IgG seropositivity until >7 months after symptom onset. However, many of their plasma samples showed insufficient neutralizing activity to maintain a protective barrier [26], and the development of neutralizing antibodies may be related to the activation of SARS-CoV-2-specific T cells and NK cells [27]. Therefore, the maintenance of long-term immunity to SARS-CoV-2 may demand a synergistic humoral and cellular immune response, and medical management is highly required. Moreover, the metabolic state of patients is important for immune response and prognosis in COVID-19. Indeed, abnormal metabolic conditions, such as obesity and diabetes, have been associated with increased mortality and long-term sequelae in COVID-19 by affecting immune responses due to increased inflammation and impaired energy generation [28]. A previous metabolomic study of patients with COVID-19 suggested that 204 metabolites might be correlated with the severity of COVID-19, and metabolic pathways and plasma metabolites are associated with inflammation and immune activation. These metabolomic data show that >100 metabolites including amino acids and their derivatives and >100 lipids including glycerophospholipids, sphingolipids, and fatty acids are decreased in the patient sera [29]. Furthermore, CFS/ME is a consequence of hypometabolic response to environmental stress, and several metabolic pathways are shown to be impaired with abnormal metabolite levels in the plasma of patients with CFS/ME [30,31]. Therefore, metabolic function and immune response caused by changes due to COVID-19 may be responsible for the sequelae, and in the present study we will investigate the effects of herbal medicine on changes in COVID-19 to provide an insight into the preparation of medical management for post-acute sequelae of SARS-CoV-2 infection.

Considering this situation, in the present study, we will administer the herbal medicines for 12 weeks maximum to patients who have fatigue or cognitive dysfunction after COVID-19 recovery, and will explore the symptom improvement associated with herbal medicine and its effect on metabolites and immune response in the peripheral blood sample. The present study might suggest the feasibility of clinical studies for herbal medications to treat post-acute sequelae following COVID-19 recovery; nevertheless, further randomized-controlled trials with sufficient sample size should be executed to establish clinical evidence on their effectiveness and safety.

## Figures and Tables

**Figure 1 healthcare-10-01839-f001:**
[figure not shown]
Flow diagram and schedule.

**Table 1 healthcare-10-01839-t001:** Schedule summary.

Visit	0	1	2	3	4	5	6	UV *
Week	−7	1	5	9	13	25	37	-
Visit Window	-	2	±7	±7	±7	±7	±7	-
Informed consent for the study	●							
Demographic information	●							
Participation in other clinical trials	●							
Medical history	●							
Confirmation of diagnosis of COVID-19 infection	●							
Medication history	●							
Vital signs	●	●	●	●	●	●	●	●
Electrocardiogram	●				●			●
Laboratory test	●				●			●
Blood collection for immune response and metabolite analysis	●				●	●	●	●
Pregnancy **	●							
Evaluation of fatigue or brain fog	●							
CIS	●		●	●	●	●	●	●
VAS (0–100) score for fatigue or brain fog	●		●	●	●	●	●	●
Inclusion/exclusion criteria	●							
KM syndrome differentiation		●						
Prescription of herbal medicine ***		●	○	○				
Drug adherence			●	●	●			●
Check for combination therapy			●	●	●	●	●	●
ChFQ		●	●	●	●	●	●	●
EQ-5D-5L		●	●	●	●	●	●	●
PSQI-K		●	●	●	●	●	●	●
K-MoCA		●	●	●	●	●	●	●
CFQ		●					●	●
BDI		●	●	●	●	●	●	●
Digit span test in K-WAIS (DF, DB, and DF-DB)		●			●	●	●	
K-BNT-15		●			●	●	●	
Adverse events check		●	●	●	●	●	●	●

●, check on visit; ○, if applicable * UV, unscheduled visit (), ** only fertile women, *** Evaluation for the continuation of herbal medicine administration at 5th and 9th weeks.

**Table 2 healthcare-10-01839-t002:** KM syndrome differentiation for allocation to treatment group.

	Fatigue		Cognitive Dysfunction
Code	CV1	CV2	CV3
Syndrome differentiation classification	Spleen-lung qi deficiency pattern	Dual deficiency of qi and yin pattern	Heart yin deficiency heat pattern
Symptom	Fatigue, appetite loss, cold sweat, shortness of breath, chest tightness, anxiety and others	Fatigue, dry cough and others	Forgetfulness, fever, insomnia, heart palpitation, stomatitis, tongue needles and others
Tongue diagnosis	Pale tongue, thin white fur	Dry mouth, dry tongue	Red tongue and low tongue coated
Pulse diagnosis	Vacuous, large, weak pulse/surging, large pulse	Fine pulse/vacuous, weak pulse	Fine, rapid pulse
Urine/feces	Difficult stool to pass/sloppy stool	Dry stool	Inhibited stool/sloppy stool

## Data Availability

This study was registered in the national clinical trial registry Clinical Research Information Service, which is a primary registry of the World Health Organization International Clinical Trials Registry Platform (KCT0006252).
